# The importance of albumin infusion rate for plasma volume expansion following major abdominal surgery – AIR: study protocol for a randomised controlled trial

**DOI:** 10.1186/s13063-016-1714-5

**Published:** 2016-12-07

**Keywords:** Albumin, Infusion rate, Plasma volume expansion, Permeability, Transcapillary escape rate

## Abstract

**Background:**

Administration of fluids to restore normovolaemia is one of the most common therapeutic interventions performed peri-operatively and in the critically ill, but no study has evaluated the importance of infusion rate for the plasma volume-expanding effect of a resuscitation fluid. The present study is designed to test the hypothesis that a slow infusion of resuscitation fluid results in better plasma volume expansion than a rapid infusion.

**Methods/design:**

The study is a single-centre, assessor-blinded, parallel-group, randomised prospective study. Patients over 40 years of age admitted to the post-operative care unit after a Whipple procedure or major gynaecological surgery and presenting with signs of hypovolaemia are eligible for inclusion. Patients are randomised in a 1:1 fashion with no stratification to either rapid (30 minutes) or slow (180 minutes) infusion of 5% albumin at a dose of 10 ml/kg ideal body weight. Plasma volume is measured using ^125^I human serum albumin at baseline (prior to albumin infusion) as well as at 30 minutes and 180 minutes after infusion start. The primary endpoint is change in plasma volume from baseline to 180 minutes after the start of 5% albumin infusion. Secondary endpoints include the integral of plasma volume over time from baseline to 180 minutes after the start of the infusion and transcapillary escape rate of albumin (%/h) from 180 minutes to 240 minutes after the start of albumin infusion. In addition, diuresis, change in central venous oxygen saturation, lactate and blood pressure will be evaluated. A total of 70 patients will be included in the study, and the study has 80% power to detect a difference of 4 ml/kg in plasma volume expansion between the two groups.

**Discussion:**

The present study is the first clinical investigation of the importance of infusion rate for the plasma volume-expanding effect of a resuscitation fluid.

**Trial registration:**

EudraCT identifier: 2013-004446-42. Registration date: 20 December 2013.

ClinicalTrials.gov identifier: NCT02728921. Registration date: 31 March 2016.

**Electronic supplementary material:**

The online version of this article (doi:10.1186/s13063-016-1714-5) contains supplementary material, which is available to authorized users.

## Background

Major surgery initiates a systemic inflammatory response syndrome (SIRS), which disrupts the normal regulation of transcapillary fluid exchange with tissue oedema and hypovolaemia as a consequence. Hypovolaemia will amplify the inflammatory reaction by reducing cardiac output and oxygen delivery, which creates a vicious circle. Fluid therapy is therefore a cornerstone in the peri-operative treatment of patients undergoing major surgery as well as in patients with increased vascular leakage of other aetiologies. However, even if fluid therapy is life-saving, it is also associated with side effects such as further oedema formation, coagulopathy and further endothelial dysfunction. Several studies indicate that these side effects may adversely affect outcome following surgery [1, 2]. Also, in other patient groups with SIRS in the intensive care unit (ICU), it has been shown that fluid overload is associated with increased incidence of respiratory failure and worse outcome [3–6].

From a clinical perspective, it is therefore important that the fluid administered to antagonize hypovolaemia remains intravascular as far as possible. Colloids are macromolecules for which the vessel wall has a low permeability, and proponents of colloids argue that less volume is required for equal plasma volume compared with crystalloids. However, extravasation of colloids not only is a function of the vessel wall permeability but also is dependent on the volume of fluid that is filtered across the capillary wall, which in turn depends on the transcapillary hydrostatic pressure [7]. In addition, transient hypervolaemia induced by rapid administration of colloids may induce increased release of the permeability-increasing diuretic agent atrial natriuretic peptide and components of the endothelial glycocalyx [8, 9].

Taken together, these data indicate that slow administration may reduce extravasation of colloids by minimizing transient hypervolaemia and transient increases in hydrostatic pressure. This hypothesis is supported by results derived from two animal model studies of sepsis-induced systemic inflammatory response showing that the plasma volume expansion was greater in animals randomised to receive a slow infusion than in those randomised to receive a rapid infusion of the same volume of colloid [10, 11].

Fluid administration is one of the most common therapeutic interventions in ICUs and in post-operative units around the world [12], and a fluid bolus is a recommended method to assess fluid responsiveness. However, to date, no study has addressed the importance of infusion rates in a clinical setting. Although rapid correction of hypovolaemia makes intuitive sense, the need for further knowledge in this aspect of fluid resuscitation was highlighted by the recent Fluid Expansion as Supportive Therapy trial, which showed a surprising increase in mortality following a rapid administration of resuscitation fluids compared with less aggressive fluid resuscitation [13]. Based on these considerations, the primary objective of the present study is to test the hypothesis that plasma volume expansion of a given volume of colloid is greater if fluid is administered slowly rather than rapidly.

## Methods/design

We are conducting a single-centre, investigator-initiated, prospective, parallel-group, randomised study of two different albumin infusion rates in patients following major abdominal surgery. The study is approved by the regional ethical vetting board in Lund, Sweden (Dnr 2014/15), and will be conducted at Skåne University Hospital in Lund. Overviews of the trial design according to the Standard Protocol Items: Recommendations for Interventional Trials (SPIRIT) statement and an overview of patient flow through the study are presented in Table 1 and Fig. 1, respectively. A SPIRIT checklist is provided in Additional file 1. Informed consent will be obtained non-consecutively from eligible participants when a member of the research team is available. The length of the study will be from signing of informed consent until 36 ± 7 days after the start of infusion of the test substance. All patients will be followed by a study investigator in a visit at the trial centre. All patients will be evaluated with regard to potential adverse effects by one of the investigators. The first patient was included on 18 June 2014. The protocol has been amended two times. The first amendment extended inclusion criteria to also include post-operative patients after major gynaecological surgery to promote recruitment. The second amendment changed the interim analysis plan by adding the Haybittle-Peto approach for the testing of efficacy. In addition, ongoing vasopressor and inotropic therapy was omitted as an exclusion criterion. The first amendment was made after 1 patient had been included, and the second was made after 24 patients had been included. The amendments were approved by both the regional ethical vetting board and the Swedish Medical Products Agency (MPA), and the current protocol version 1.3 2015-04-03 was approved by MPA 2015-05-27.

**Table 1 Tab1:** Overview of enrolment, interventions and assessments according to the SPIRIT (Standard Protocol Items: Recommendations for Interventional Trials) statement

	Study period							
	Enrolment	Allocation	Post-allocation					Close-out
Time point	-t_1_	0	t_1_	t_2_	t_3_	t_4_	t_5_	t_6_
Enrolment								
Eligibility screen	X							
Informed consent	X							
Allocation		X						
Interventions								
Infusion of 5% albumin (10 ml/kg) over 30 minutes				X				
Infusion of 5% albumin (10 ml/kg) over 180 minutes				X				
Assessments								
Plasma volume			X	X	X			
Transcapillary escape rate of albumin						X		
Haemodynamic data, haematocrit, lactate, ScvO_2_	X		X	X	X			
Post-operative complications			X	X	X	X	X	
Adverse events, serious adverse events			X	X	X	X	X	X

*Abbreviations: ScvO*
_*2*_ Central venous oxygen saturation, *t*
_*1*_ Baseline, *t*
_*2*_ Start of albumin infusion, *t*
_*3*_ 180 minutes after start of albumin infusion, *t*
_*4*_ 180–240 minutes after start of albumin infusion, *t*
_*5*_ 30 days after operation, *t*
_*6*_ 36 ± 7 days after inclusion or until resolution of any adverse event, serious adverse event or suspected unexpected serious adverse reaction

**Fig. 1 Fig1:**
[figure not shown]
Detailed enrolment and randomisation flowchart for Albumin Infusion Rate (AIR) study. *PACU* Post-anaesthesia care unit, *ScvO*
_*2*_ Central venous oxygen saturation, *MAP* Mean arterial pressure

### Inclusion criteria

Post-operative patients following non-emergent operation ad modum Whipple procedure or major gynaecological cancer surgery at the age of 40 years or older will be included if fulfilling the following criteria:Indication for fluid therapy as judged by the physician caring for the patient and at least one of the following criteria is fulfilled within 5 h after admission to the post-anaesthesia care unit (PACU):Positive ‘leg-raising test’ (pulse pressure increase >9% or stroke volume increase by >10% as measured with cardiac ultrasound [14]Central venous oxygen saturation (ScvO_2_) <70%Plasma lactate >2.0 mmol/LUrine output <0.5 ml/kg in the hour prior to inclusionRespiratory variation of the inferior vena cava >15% as measured by ultrasound [15, 16]Systolic blood pressure <100 mmHg or mean arterial blood pressure <55 mmHg
Written consent by the patient to participate in the study obtained prior to operation

### Exclusion criteria

Patients fulfilling any of the following criteria will be excluded from the study:Hypersensitivity to the active drug or the tracerSigns of post-operative bleedingHistory of heart failureThe physician caring for the patient considers that there are strong reasons to administer another fluid, or the same fluid but in another way or in a different volume than stated in the protocolPregnancyClinical judgement by the investigator or the treating physician that the patient should not participate in the study for reasons other than described above

### Informed consent and withdrawal

Patients scheduled for the operative procedures described above will be assessed for inclusion. If none of the pre-operative exclusion criteria are met, a member of the research team will provide both oral and written information before surgery (Additional file 2). All patients will be given the opportunity to ask questions about the study and will also be given sufficient time to decide whether to participate. Patients are informed of their right to withdraw from the study at any time. A patient who withdraws consent receives standard care. In addition, the patient/participant may be permanently withdrawn at the investigator’s or the treating physician’s discretion at any time if this is considered to be in the patient’s best interest. Predefined permanent withdrawal criteria are as follows:Change of surgery procedure to other than operation ad modum Whipple or major gynaecological cancer surgerySerious violation of the study protocol, such as administration of other resuscitation fluid in a volume >200 ml within 3 h after start of albumin infusionOccurrence of known side effects, defined as serious adverse events (SAEs) listed in the summary of product characteristics of 5% albumin or SERALB-125® (IBA-CIS Bio International, Gif-Sur-Yvette, France) (Side effects that warrant permanent withdrawal include anaphylactic shock or pulmonary oedema.)

A record is kept of patients who consented in the pre-operative screening but were never enrolled (patient screening log).

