### Secondary outcomes

Secondary outcomes are differences in plasma volume over time (integral of plasma volume over time from the start of albumin infusion from plasma volume PV1 to PV3) and incidence of post-operative complications up to 30 days post-operatively (see Additional file 3 for definitions of complications). Other outcomes of interest are TER for albumin from 180–240 minutes after the start of albumin infusion, change in heart rate, change in central venous oxygen saturation, change in haemoglobin concentration in blood, change in blood pressure, change in central venous pressure, change in plasma lactate from the start of albumin infusion to 3 h after start of infusion, and diuresis from the start of albumin infusion to 3 h after the start of infusion.

In addition, exploratory analyses are planned. These analyses include measurement of effects of the different infusion rates on plasma concentration of markers of endothelial damage and on hormones involved in fluid homeostasis. For this purpose, blood samples are collected 5 minutes before centrifugation, and plasma samples will be stored following centrifugation at −80 °C until analysis. We also intend to analyse to what extent included patients are hypovolaemic at inclusion (>10% lower than calculated normal blood volume [18]).

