### Statistical analysis plan

The study will continue until the planned number of patients has been included, unless the interim analysis indicates that the study should be stopped. Results will be unblinded when all data have been collected. Only patients who received 90% or more of the intended dose will be included in the analysis. The investigating team will perform the statistical analyses.

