#### General analytical principles

Analysis will be performed on a per-protocol basis.All hypothesis tests will be two-sided, with a maximal type I error risk of 0.05.Subgroup analysis will be performed regardless of overall treatment efficacy.Imputation will not be used to correct for missing data in the analysis.

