#### Analysis of outcomes

The primary outcome will be analysed using Student’s *t* test. Secondary outcomes will be analysed using Student’s *t* test or the Mann-Whitney *U* test as appropriate. Differences between the groups will be reported as means with 95% confidence intervals. In the event of no difference between the groups with regard to primary outcome and a difference in the secondary outcome of plasma volume over time, we will interpret these results as supporting our hypothesis but that confirmatory studies are needed. With the exception of number of complications, all other outcomes are regarded as exploratory, and no emphasis will be placed on differences between the treatment groups, should the primary outcome and plasma volume over time outcome be negative.

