### Harms

All patients are evaluated with regard to potential AEs or SAEs by one of the investigators, and potential AEs and SAEs are recorded in the CRF. A SAE is defined as an event that fulfils one or more of the following criteria: results in death, is life-threatening, requires prolongation of hospitalisation, results in persistent or significant disability or incapacity or any other important medical event. The investigator evaluating the patient at the end of the study is responsible for the treatment of any AE or SAE until resolution of the AE or SAE. Depending on the nature of the AE or SAE, the treatment will take place at either the trial centre, the local hospital or as an outpatient. If the responsible investigator/sponsor judges the SAE as being drug-related and unexpected, this must be promptly reported to the sponsor, which is responsible for reporting suspected unexpected serious adverse reactions to the Swedish MPA and the regional ethical vetting board.

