### Trial status

Recruitment has been completed. The interim analysis has been performed, and no reason to halt the study has been found. No SAEs have been registered to date.

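### The single per-protocol, ≥90%-dose analysis basis also covers 30-day complications, so that comparison can leave out patients because of a harm the infusion may have caused

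*Protocol article*

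**What the plan says.** Four statements in the protocol article bear on this point.

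- **Withdrawal.** Informed consent and withdrawal lists predefined reasons for permanent withdrawal. One is a known side effect of the albumin or the tracer at the level of a serious adverse event: "Side effects that warrant permanent withdrawal include anaphylactic shock or pulmonary oedema".
- **Analysis set.** General analytical principles states: "Analysis will be performed on a per-protocol basis". Statistical analysis plan adds: "Only patients who received 90% or more of the intended dose will be included in the analysis". No outcome is exempted from either rule. On missing values: "Imputation will not be used to correct for missing data in the analysis".
- **The outcome affected.** Secondary outcomes includes "incidence of post-operative complications up to 30 days post-operatively", with definitions left to an additional file that is not shown. Analysis of outcomes gives complications a special standing: "With the exception of number of complications, all other outcomes are regarded as exploratory".
- **Harms recording.** Harms states: "All patients are evaluated with regard to potential AEs or SAEs by one of the investigators". Methods/design has every patient followed to 36 ± 7 days after the start of infusion. Trial status reports recruitment complete and the interim analysis done, and adds: "No SAEs have been registered to date".

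**The concern.** For the plasma-volume question, a per-protocol set has a rationale: the trial asks how well a given volume expands plasma, and a patient who did not get that volume says little about it. Complications are different. Pulmonary oedema or anaphylactic shock occurs after randomisation and may be a consequence of the infusion. If such a patient leaves the analysis set, a harm outcome is compared only among patients selected partly for not having had a harm. Randomisation no longer protects that comparison, and the bias can run in either direction.

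Complications also keep their weight when both plasma-volume results are negative. The trial has no data monitoring board (Auditing), and the interim analysis looks only at efficacy and futility (Interim analysis). The final between-arm comparison is therefore the only one the article plans for complications, and its population matters.

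**Working it through.** The article gives no complication, pulmonary oedema or anaphylaxis rate, so there is no figure of its own to reproduce. The check has three parts.

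**1. What the rules imply when read together**

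| Situation of a treated patient | 90% dose rule | Per-protocol basis |
|---|---|---|
| Withdrawn for a serious side effect, under 90% of dose given | Excluded | Excluded on a plain reading |
| Withdrawn for a serious side effect, at least 90% given | Passes | Not stated; a permanently withdrawn patient would ordinarily not count as per protocol |
| Not withdrawn, full dose | Passes | Included |

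The first row is settled by the text. The second is open. In neither of these rows does the plan say that the patient's complications still count.

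**2. Whether the dose rule treats the arms alike**

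Inputs: infusion over 30 or 180 minutes (Study interventions) and the 90% threshold (Statistical analysis plan). A constant rate is assumed.

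- Rapid arm: 0.9 × 30 = 27 minutes.
- Slow arm: 0.9 × 180 = 162 minutes.

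Take an event at 60 minutes that ends the infusion. The rapid-arm patient has had the whole dose and passes. The slow-arm patient has had 60/180 = 33% and fails. Between 27 and 162 minutes, an event that stops the infusion fails the rule only in the slow arm. With 35 per arm, one patient is 1/35 = 2.9 percentage points.

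**3. How much a comparison could change (assumed rates)**

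Let h be the risk of a harm that triggers withdrawal and c the risk of any other complication. Take c as equal in both arms and independent of h, and suppose the harm counts as a complication. The risk of at least one complication among all treated patients is

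1 − (1 − h)(1 − c),

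so the difference between arms is (h_rapid − h_slow)(1 − c). If every patient with such a harm is removed, the remaining risk is c in each arm and the difference is 0.

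| Assumed harms, rapid vs slow | c = 20% | c = 40% | After removal |
|---|---|---|---|
| 2/35 vs 0/35 | 2/35 × 0.8 = 4.6 points | 2/35 × 0.6 = 3.4 points | 0 |
| 5/35 vs 1/35 | 4/35 × 0.8 = 9.1 points | 4/35 × 0.6 = 6.9 points | 0 |
| 0/35 vs 0/35 | 0 | 0 | 0 |

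The first two rows are illustrations, not estimates. The last row matches what the article reports for serious events: with none, this withdrawal criterion removes nobody and the two analyses agree.

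**The case against.** The strongest reply is that the plan does not say these patients are dropped. The only explicit inclusion rule is the dose, and a rapid-arm patient satisfies it from 27 minutes on. Adverse events and serious adverse events are assessed and recorded in everyone up to close-out. The planned CONSORT diagram shows numbers randomised and completing in each arm, so losses would be visible. The complication definitions are not shown, so it cannot be confirmed that infusion-related pulmonary oedema or anaphylaxis would count. No serious event had been registered.

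All of this stands, and it limits the point in three ways.

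- A reader might infer that the complication comparison does omit these patients, or that a harm would disappear from the trial. The documents support only that the comparison can leave them out. The record of harms would remain.
- A reader might infer that these are the harms most likely to differ by infusion rate. Background links fluid overload, not rate, to respiratory failure, and does so in other intensive-care patients. Nothing ties anaphylactic shock to rate.
- A reader might also object to Student's t test or Mann-Whitney for an incidence, because Fisher's exact test can give a very different p-value: for 1/35 vs 6/35, 0.047 by t test and 0.106 by Fisher. That does not show the planned test to be invalid. Exact enumeration at 35 per arm gives the t test a type I error of about 1.4% to 5.7% for event rates of 3% to 50%, against 0.04% to 2.8% for Fisher. The gap mainly reflects Fisher's conservatism, so the choice is a trade-off. The plan also calls the outcome a number of complications, for which a rank test is defensible.

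What the reply does not remove is that one population is stated for every outcome, with no exception for harms. That is a stated choice, not a detail left to a fuller document.

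**Conclusion.** The concern holds as a risk of bias. A complication outcome that the plan sets apart from the exploratory ones is placed on an analysis basis that can exclude patients because of a harm treatment may have caused. The dose rule can also exclude differently by arm, in the window from 27 to 162 minutes at a constant rate.

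Under the assumed rates above, the hidden difference would be about 3.4 to 9.1 percentage points. This rests on three assumptions: all affected patients are removed, the harms count as complications, and other complications are equal between arms. With no serious adverse event registered, there is no documented effect of the side-effect criterion. Zero serious events does not settle the other routes out of the set, such as withdrawal at a clinician's discretion or after more than 200 ml of another resuscitation fluid, and the article gives no counts for these.

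The point is worth correcting before unblinding. It concerns a secondary outcome, leaves the primary plasma-volume analysis untouched and is of moderate weight.

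**What to change.** Before unblinding, amend the analysis principles as follows.

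- Limit the per-protocol, 90%-dose set to the plasma-volume and physiological outcomes.
- Compare complications and adverse events in all randomised patients who received any study infusion, by allocated arm. Include withdrawn patients, followed to day 30 unless they withdrew consent for follow-up.
- Report the number and percentage with at least one complication per arm, and a risk difference with a 95% confidence interval.
- State how many patients each withdrawal criterion and the dose rule removed in each arm.

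This does not touch the withdrawal criteria themselves, which are a clinical matter. The cost is a few sentences. Follow-up of all patients to 36 ± 7 days and recording of adverse events in everyone are already planned, so no new data collection is needed. Recruitment is complete, but the article has results unblinded only once all data are collected, so the change can still be made without knowledge of the results if unblinding has not yet taken place.
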